#### 4.1 Sample Size Calculation

##### 4.1.1 Method of Sample Size Calculation

There are 3 arms in this study: Intervention arm 1 (TQB2450, Anlotinib, Carboplatin, and Etoposide); Intervention arm 2 (TQB2450 placebo, Anlotinib, Carboplatin, and Etoposide); Control arm (TQB2450 placebo, Anlotinib placebo, Carboplatin, and Etoposide). The primary efficacy endpoints of this trial are PFS and OS. In this study, a fixed-sequence test will be used for comparisons between treatment groups.

The safety analysis and re-estimation of sample size will be conducted by the Independent Data Monitoring Committee (iDMC). The re-estimation of sample size based on PFS is planned after 50% of the planned PFS events (174 cases). At the same time, a safety analysis will be performed. The interim analysis will be conducted by iDMC. One interim analysis for OS is planned for this study after 70% of the planned OS events. If expected efficacy is observed, early declaration of the study due to efficacy would be considered. The interim analysis will be conducted by iDMC.

The previous study showed that the median OS and PFS in the control arm were 10 and 4 months, respectively [5]. Patients were enrolled within a 12-month accrual period with an 18-month follow-up and were randomly assigned (1:1:1) to three groups. The power was 85% with a type I error rate of 0.050 and a dropout incidence of 10%. The type I error rate in the interim analysis for PFS will be controlled by the Method Based on the Sum of P-values (MSP). The initial sample size in this study will be estimated based on PFS using a computer simulation program.

##### 4.1.2 Sample Size Estimation in the Intervention Arm 1

Assuming that the HR for PFS in the intervention arm 1 compared with the control arm is 0.6, the hazard rate in the intervention arm 1 is 0.1040, and that in the control arm is 0.1733 along with exponential distribution. Approximately 165 PFS events are expected if 174 patients are enrolled. A total of 194 patients are recruited and randomly assigned (1:1) to intervention arm 1 and control arm, considering an approximate dropout incidence of 10%. The interim analysis will be conducted when the planned PFS events are ~83. The final analysis will be performed after ~165 of the planned

PFS events.

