#### **4.1.3 Sample Size Estimation in the Intervention Arm 2**

Assuming that the HR for PFS in the intervention arm 2 compared with the control arm is 0.65, the hazard rate in the intervention arm 2 is 0.1126, and that in the control arm is 0.1733 along with exponential distribution. Approximately 231 PFS events are expected if 242 patients are enrolled. A total of 270 patients are recruited and randomly assigned (1:1) to intervention arm 2 and control arm, considering an approximate dropout incidence of 10%. The interim analysis will be conducted when the planned PFS events are ~116. The final analysis will be performed after ~231 of the planned PFS events.

Assuming that the HR for OS in intervention arm 2 compared with the control arm is 0.72, 331 OS events are expected with the type I error rate of 0.050 if 442 patients are enrolled. A total of 492 patients were recruited and randomly assigned (1:1) to intervention arm 2 and control arm, considering an approximate dropout incidence of 10%.

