**Cycle 4 and subsequent even cycles (Vital signs and physical examination will be measured before administration on C4D1)**

- Day 21 on every cycle:

Vital signs, ECOG PS, physical examination;

Imaging examination (CT or MRI), CEA, NSE;

12-lead electrocardiogram;

Blood biochemistry, hemanalysis, urinalysis and stool tests (including occult blood), thyroid function, coagulation function, blood lipase, and amylase;

Biomarkers of myocardial injury;

Echocardiography;

Adrenal cortex function;

Questionnaire for HRQOL;

Concomitant medications, AEs, medication allocation, and recall.

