**Post-treatment Follow-ups**

All subjects will be followed up every 8 weeks (including telephone follow-up) to collect data on other antitumor therapy and disease status. The treatment regimens, cycles, and outcomes of any other treatment must be recorded during the trial. Post-treatment follow-up will be conducted until

death. Reasons and the date of death will be recorded for overall survival analysis.

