## 11. QoL

The QoL will be evaluated from various aspects through questionnaires. The exploratory objective of this trial is to evaluate the HRQOL, aiming to collect information on drug application as early as possible. The questionnaires for HRQOL will be completed at the scheduled time point.

To avoid being influenced by the investigator(s) or new conditions, the questionnaire should be

completed before any clinical examination and evaluation, as well as any new disease information and new treatment. The questionnaire will be stored as source documents.

Investigator(s) will review the questionnaire and evaluate the clinical signs. Any unobserved AEs in clinical evaluation will be recorded in the CRF.

The EuroQol five-dimensional (EQ-5D) descriptive system consists of a questionnaire and utility value conversion table. The questionnaire is reported for health conditions and EQ visual analog scale (EQ-VAS) score, while the utility value conversion table is reported for EQ-5D index values.

The questionnaire contains EQ-5D health state classifications and EQ-VAS. EQ-5D health state classification contains 5 dimensions, including mobility, self-care, usual activities, pain discomfort, and anxiety/depression. Each dimension contains 3 levels, including no problems, some problems, and extreme problems. EQ-VAS is a 20 cm vertical visual analog scale. 100 at the top indicates the best health you can imagine and 0 at the bottom indicates the worst imaginable health state.

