##### **➤ DOR**

The median DOR will be estimated using the Kaplan-Meier method and presented with the Kaplan-

Meier curve. The comparison of DOR between intervention arms will be performed using a stratified log-rank test. DOR will be only analyzed in responders.

➤ **DCR**

The number and percentage of subjects with the disease control (PR, CR, or SD) will be presented. The DCR and corresponding 95%CI will be summarized using F-distribution by binomial probabilities. The difference in DCR between intervention arms will be compared by the stratified CMH test. Stratification factors as items specified in section 4.3.

➤ **6-month and 12-month PFS rates**

The PFS rate and the corresponding 95%CI for each intervention arm will be estimated using the Kaplan-Meier method and compared with Fisher's Exact Test.

➤ **12-month and 18-month OS rates**

The OS rate and the corresponding 95%CI for each intervention arm will be estimated using the Kaplan-Meier method and compared with Fisher's Exact Test.

➤ **HRQOL**

HRQOL will be summarized by descriptive statistics. The changes of each item from baseline at each scheduled visit will be summarized by mean, SD, median, minimum, and maximum within each intervention arm. The grade of each item will be presented by the number and percentage and compared with the Wilcoxon rank sum test between intervention arms.

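### EQ-5D item grades are compared by an unadjusted Wilcoxon test although baseline grades are collected; if the test is run by visit, later visits compare unequally selected patients

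*Protocol*

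**What the plan says.** Section 7 of the protocol schedules the EQ-5D form at screening, on day 21 of cycle 2, on day 21 of cycle 4 and later even cycles ("Questionnaire for HRQOL"), and at end of treatment. Imaging falls on the same day-21 visits. After treatment the plan is: "All subjects will be followed up every 8 weeks (including telephone follow-up) to collect data on other antitumor therapy and disease status". Death is also recorded, but no HRQOL form is listed.

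Under section 5.2.1, treatment ends at progression, unacceptable toxicity, loss of benefit or by the investigator's decision. Section 5.4 has RECIST progression checked against iRECIST before further treatment is decided.

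Section 13.4.2 first describes HRQOL, with changes from baseline summarised within each arm at the scheduled visits. The between-arm test follows: "The grade of each item will be presented by the number and percentage and compared with the Wilcoxon rank sum test between intervention arms". No visit, covariate or stratum is named for it. In the same section ORR and DCR are compared by a stratified CMH test and DOR by a stratified log-rank test.

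Sections 2 and 3.6 list quality of life as a secondary objective and endpoint, and section 13.2.2 applies a two-sided 0.05 level to secondary efficacy endpoints. Section 11 says instead: "The exploratory objective of this trial is to evaluate the HRQOL".

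**The concern.** There are three separate issues.

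- **The test leaves out information the trial collects.** Baseline grade and the three stratification factors (ECOG PS, brain metastases, liver metastases) are known for randomised patients. Comparing raw grades without them is not invalid in a complete randomised comparison. It gives up precision, though, and it cannot account for baseline differences once patients start to leave.
- **Still being due a form is a post-randomisation outcome that the treatments are meant to change.** At a late visit the patients who supply a form are a selected part of each arm, and the selection is stronger where progression is faster. A by-visit test there no longer has the protection of randomisation.
- **The label is inconsistent.** A reader cannot tell whether an HRQOL P value is a secondary-endpoint result at the 0.05 level or an exploratory one.

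What is at stake is the HRQOL statement in the trial report: an apparent difference, or an apparent absence of one, could reflect who was left to answer.

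**Working it through.** **Inputs.** Section 4.1.1: "The previous study showed that the median OS and PFS in the control arm were 10 and 4 months, respectively". Section 4.1.2: "Assuming that the HR for PFS in the intervention arm 1 compared with the control arm is 0.6", and "the hazard rate in the intervention arm 1 is 0.1040, and that in the control arm is 0.1733 along with exponential distribution". Section 4.1.3 assumes an HR of 0.65 for arm 2: "the hazard rate in the intervention arm 2 is 0.1126, and that in the control arm is 0.1733 along with exponential distribution". Cycles last 21 days. Total 738, allocated 1:1:1, so 738/3 = 246 per arm. A month is taken as 30.4375 days (my convention).

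**Step 1: reproduce the plan's hazards.** Hazard = ln 2 / median. Control: 0.6931/4 = 0.1733. Arm 1: 0.6 × 0.1733 = 0.1040. Arm 2: 0.65 × 0.1733 = 0.1126. All three agree with the protocol.

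**Step 2: progression-free share at each HRQOL visit.** S(t) = exp(−hazard × t), with t = 21 × cycle / 30.4375 months. For cycle 8, t = 168/30.4375 = 5.52, so control is exp(−0.1733 × 5.52) = 38.4% and arm 1 is exp(−0.1040 × 5.52) = 56.3%.

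| Day 21 of cycle | t (months) | Control | Arm 1 | Arm 2 |
|---|---|---|---|---|
| 2 | 1.38 | 78.7% (194) | 86.6% (213) | 85.6% (211) |
| 4 | 2.76 | 62.0% (152) | 75.1% (185) | 73.3% (180) |
| 6 | 4.14 | 48.8% (120) | 65.0% (160) | 62.7% (154) |
| 8 | 5.52 | 38.4% (95) | 56.3% (139) | 53.7% (132) |
| 12 | 8.28 | 23.8% (59) | 42.3% (104) | 39.4% (97) |

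In brackets: the approximate number out of 246. With 30-day months the cycle-8 figures for control and arm 1 are 38% and 56%; with 28-day months they are 35% and 54%.

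**Step 3: from progression-free to due a form.** The form falls on the same day as the scan, and section 11 has it completed before examination and evaluation. A patient whose progression is found on the cycle-8 scan is therefore still due a cycle-8 form. The share due that form lies roughly between the cycle-6 and cycle-8 rows: control 38% to 49%, arm 1 56% to 65%, a gap of about 16 to 18 points. By the same argument, cycle 4 lies between the cycle-2 and cycle-4 rows: control 62% to 79%, arm 1 75% to 87%, a gap of about 8 to 13 points. Treatment past RECIST progression raises these shares. Deaths, progressions found between scheduled scans, toxicity stops and withdrawals lower them.

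**Step 4: could this matter to the test?** No figure in the protocol links item grade to progression, so this is illustration only. Both models compare control with arm 1, give treatment no effect on the item, use a three-level grade and 246 per arm, and let patients leave only by progression.

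- Correlation between the latent grade and progression time of 0, 0.2, 0.4 and 0.6: the nominal 5% Wilcoxon test at cycle 8 rejects in 4.8%, 7.1%, 13.1% and 26.7% of trials. With a positive correlation, control looks better.
- Log-normal frailty with variance 0.25 to 1.0 and correlation 0.3 to 0.6 between grade and log-frailty: rejection is 5.3% to 9.3% at cycle 4, 5.6% to 12.1% at cycle 8 and 5.8% to 11.4% at cycle 12.

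Both take the progression-free patients at the visit as those with a form, which Step 3 shows is only a proxy.

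**The case against.** The strongest case against has several parts.

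- **The Wilcoxon sentence names no visit or population.** This stands as a limit. Scheduled visits are mentioned in the preceding sentence, on within-arm change, and section 13.1 assigns all efficacy analysis to the ITT set. Testing by visit is the natural reading but not the explicit one.
- **Section 3.2.2 carries the last examination results of non-completers into the final result, and an end-of-treatment form exists.** Section 3.2.2 gives no rule for HRQOL visits. Carrying an earlier grade past progression or death would not remove the selection. The end-of-treatment form is completed at different times in different arms, so it does not repair a comparison at a given cycle.
- **Adjustment and missing-form rules usually belong in the SAP.** This is true of their absence, and no finding is made of that. The protocol does, however, fix a specific unadjusted test.
- **The 38% and 56% at cycle 8 might be read as a ceiling on those still on treatment.** The documents do not support that reading: treatment past RECIST progression is possible, and the form is due on the day of the scan.
- **A reader might infer that the test must show a false HRQOL deficit for the active arms.** That does not follow. It needs sicker patients to progress sooner and progression to be the main exit. Toxicity exits also differ by arm: Supplementary Table S3 gives discontinuation for treatment-emergent events as 19.9% in arm 1, 15.2% in arm 2 and 10.6% in control. These could offset the effect.
- **The consequence is small.** This stands. HRQOL is outside the fixed sequence in section 13.2.2 and is described mainly by summary statistics.

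**Conclusion.** The point holds in a limited form. The protocol fixes a raw-grade, unadjusted between-arm test although baseline grades and strata are available. Its collection schedule means that, if the test is applied by visit, later visits compare unequally selected patients. The imbalance in those due a form at cycle 8 is roughly 16 to 18 percentage points between control and arm 1. That rests on the plan's exponential hazards and on progression-free status as a proxy.

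Whether this produces a bias, how large it is and which way it goes cannot be settled from the documents. If sicker patients progress sooner, it works against the active arms; differential toxicity stops could offset that. The simulated rejection rates, from near nominal to about 27%, show that the outcome depends on the assumed link between grade and progression. The contradictory labelling of HRQOL is a plain inconsistency. The effect is confined to the interpretation of HRQOL, and the PFS and OS error rates and conclusions are untouched.

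**What to change.** 1. In section 13.4.2, replace the raw-grade Wilcoxon test with a between-arm comparison adjusted for the baseline grade and the three stratification factors, for example an ordinal repeated-measures model for the items.
2. Limit P values to the induction visits, cycles 2 and 4, where attrition is smaller though not absent.
3. Show later visits descriptively, with the number of forms expected and received in each arm.
4. Use one label for HRQOL, secondary or exploratory, in sections 3.6 and 11.

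The cost is wording and programming; no new data are needed. The downsides are that late visits carry no P values and that some selection remains at cycle 4, which adjustment reduces only as far as baseline grade and strata explain who stays.

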### **13.5 Safety Analysis**

#### **13.5.1 Treatment Exposure and Compliance**

Treatment exposure will be summarized by mean, SD, minimum, maximum, and median in each intervention arm.

Treatment exposure, the completed treatment cycle, dose adjustment and reasons, and the cumulative number of dose adjustments will be summarized.

Treatment duration, cumulative dose, dose intensity, and dosing compliance during the treatment will be statistically described.

The dosing compliance will be calculated based on the sum of all actual doses (defined as the values entered on the actual dose administered field on the eCRF) taken across the treatment period and the sum of protocol-defined doses.

#### **13.5.2 AEs**

All AEs will be coded using the Medical Dictionary for Regulatory Affairs (MedDRA) for safety analysis.

An overview table of AEs will be provided for each intervention arm by the MedDRA preferred term (PT) and primary system organ class (SOC), including the number of events and the number (incidence) of subjects with the following: all AEs, AEs before the first dose, treatment-emergent AEs (TEAEs), significant TEAEs, TEAEs of special interest, TEAEs with grade 3 or more, serious

TEAEs (SAEs), treatment-related TEAEs, treatment-related SAEs, TEAEs leading to dose adjustment, treatment discontinuation, study termination, and death.

TEAEs or treatment-related TEAEs with  $\geq 5\%$  incidence will also be summarized by PT.

Treatment-related TEAEs with grade 3 or above (as per NCI-CTCAE criteria) will also be summarized by PT.

TEAEs or treatment-related TEAEs with  $\geq 10\%$  incidence will also be summarized by PT.

A frequency table of AEs will be provided for each intervention arm by SOC and PT. The incidence will be calculated by the system, symptoms, and vital signs (the number of events is defined as the number of patients with at least one event).

The number (percentage) of patients with TEAEs will also be provided by severity grade per NCI-CTCAE v5.0 and the causality to the study drugs. A patient will be counted only once by the worst severity grade per NCI-CTCAE v5.0.

Listings of TEAEs and SAEs will be provided.

The incidence of TEAEs and treatment-related TEAEs between each arm will be compared with the Fisher's Exact Test, when necessary.

TEAEs of special interest and the median time of the first occurrence.

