### **Secondary objectives:**

- To compare the ORR, DCR, duration of response (DOR), 6-month PFS rate, 12-month PFS rate, 12-month OS rate, 18-month OS rate, and quality of life (QOL) across the three treatment arms.
- To compare safety and tolerability based on incidence and severity of AEs and serious adverse events (SAEs), as well as abnormal laboratory test indicators across the three treatment arms.
- To evaluate the immunogenicity of TQB2450 plus anlotinib and EC.

- To explore additional biomarkers related to efficacy, mechanisms of action, safety, and/or pathological mechanisms.

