**Criteria for dose reduction:**

Anlotinib/placebo: A maximum of two dose reductions of anlotinib (to 10/0 mg, 8/0 mg, and then discontinuation) are allowed according to drug-related AEs, but the cross-dose adjustment is not permitted. For subjects with a dose reduction to 10/0 or 8/0 mg, if subjects may experience disease progression per the investigators but still benefit from the increased dose after a period of medication, subjects could resume only one reduced dose when the safety profile is stable, but the cross-dose adjustment is not permitted.

TQB2450 injection: No dose reduction will be considered.

Efficacy is assessed every 2 cycles. Subjects with disease control and tolerable AEs will continue treatment until loss of clinical benefit, unacceptable toxicity, PD, or unsuitable continued medication as determined by the investigators.

No other antitumor therapies will be considered during the study treatment.

[figure not shown]

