**Treatment cycle:**

Treatment cycles are repeated every 21 days, with no other anticancer therapy during the medication. Patients with the disease control (CR+PR+SD) and who can tolerate adverse effects continue the medication until disease progression or intolerance.

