### (3) Type I error control for interim efficacy analysis based on OS

One interim analysis for OS is planned for this trial after 70% of the planned OS events (348 cases). If expected efficacy is observed, early declaration of the trial due to efficacy would be considered. The interim analysis will be conducted by iDMC.

Type I error will be controlled by the O'Brien-Fleming spending function approach. According to the O'Brien-Fleming spending function approach, in the interim efficacy analysis based on OS, the one-side significance level is set as  $\alpha_1 = 0.0074$  in the interim analysis and  $\alpha_2 = 0.0228$  in the final analysis.

- In the interim analysis:  $P_1 \leq \alpha_1$ , early declaration of the trial will be considered according to actual results;
- In the final analysis:  $P_2 \leq \alpha_2$ , the between-group difference in OS will be considered statistically significant.

$P_1$  = the one-side P value in the interim analysis;  $P_2$  = the one-side P value in the final analysis;

The tests sequence and type I error in the final analysis are shown in the following figure:

[figure not shown]

A two-sided test with a significance level of  $\alpha=0.05$  will be used for secondary efficacy endpoints and safety analysis. Two-sided  $P \leq 0.05$  will be considered statistically significant with a 95%CI.

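### Fisher P values on whole-treatment AE incidence cannot separate added toxicity from the longer treatment that the plan expects in the anlotinib arms

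*Protocol*

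**What the plan says.** Comparing safety across the three arms is a secondary objective (section 2): "To compare safety and tolerability based on incidence and severity of AEs and serious adverse events (SAEs". Section 13.5.2 names the test: "The incidence of TEAEs and treatment-related TEAEs between each arm will be compared with the Fisher's Exact Test, when necessary". It also says what is counted: "the number of events is defined as the number of patients with at least one event". The end of section 13.2.2 sets a two-sided 0.05 level that "will be used for secondary efficacy endpoints and safety analysis".

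Section 5.2.1 sets the length of treatment for all arms, placebo included: "Subjects with disease control and tolerable AEs will continue treatment until loss of clinical benefit, unacceptable toxicity, PD, or unsuitable continued medication". Section 5.3.1 repeats that patients with disease control who tolerate treatment "continue the medication until disease progression or intolerance".

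The sample size section assumes exponential PFS. In section 4.1.2, "the hazard rate in the intervention arm 1 is 0.1040, and that in the control arm is 0.1733"; section 4.1.3 gives 0.1126 for arm 2.

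Exposure is summarised on its own in section 13.5.1: "Treatment duration, cumulative dose, dose intensity, and dosing compliance during the treatment will be statistically described". The only time-based AE item is the median time to first occurrence, for TEAEs of special interest (13.5.2). The protocol names no exposure-adjusted rate, common window or stage-specific comparison for AE incidence.

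**The concern.** A crude proportion with at least one event grows with the time over which events are counted. If the trial works as designed, patients in the anlotinib arms stay on treatment longer than control patients. Fisher's null hypothesis is equal proportions, so for events that keep arising on treatment it is false even when the monthly event rate is identical.

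At stake is how the secondary safety comparison is read. A small P value for an anlotinib arm against control could reflect added toxicity, longer observation or both, and the named test cannot tell them apart. The primary PFS and OS results are not touched.

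**Working it through.** **Inputs.** Control median PFS 4 months, 12 months of accrual and 18 months of follow-up (4.1.1); PFS HR 0.6 for arm 1 (4.1.2) and 0.65 for arm 2 (4.1.3); 738 patients randomised 1:1:1 (4.1.4), so 738/3 = 246 per arm; induction of four 21-day cycles (5.2.1), so 84/30.44 = 2.76 months; two-sided 0.05 (13.2.2).

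**Reproducing the plan's figures.** ln 2/4 = 0.1733; 0.6 × 0.1733 = 0.1040; 0.65 × 0.1733 = 0.1126. All three match. With uniform accrual, the event probability is 1 − (e^(−18h) − e^(−30h))/(12h). It gives 0.981 for control and 0.912 for arm 1, and 174 × their mean = 164.7 (stated 165). The same formula gives 231.0 for arm 2 against control (stated 231).

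**Implied time to progression.** Means are 1/0.1733 = 5.77, 1/0.1040 = 9.62 and 1/0.1126 = 8.88 months. The ratios to control are 1/0.6 = 1.67 and 1/0.65 = 1.54. Medians are 4.0, 6.67 and 6.15 months.

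**Crude incidence at an equal AE rate.** The documents give no AE hazard. Assume one constant first-event rate λ in every arm and time on treatment equal to time to progression with hazard h. Then incidence = λ/(λ + h). At λ = 0.05, control is 0.05/0.2233 = 22.4% and arm 1 is 0.05/0.1540 = 32.5%. The probability that two-sided Fisher gives P ≤ 0.05 was enumerated exactly over both binomials, 246 per arm.

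| λ per month | Control | Arm 1 | Arm 2 | Rejects, 1 vs control | Rejects, 2 vs control | Rejects, 1 vs 2 |
|---|---|---|---|---|---|---|
| 0.01 | 5.5% | 8.8% | 8.2% | 24.7% | 17.5% | 4.1% |
| 0.05 | 22.4% | 32.5% | 30.8% | 67.5% | 51.7% | 5.7% |
| 0.10 | 36.6% | 49.0% | 47.0% | 77.1% | 61.7% | 6.2% |

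With equal exposure the same test rejects in 3% to 4% at these rates. Over a wider range, rejection peaks at 78% (arm 1) and 63% (arm 2) when control incidence is 40%, and falls to 14% and 11% when it is 95%.

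**Varying the assumptions (arm 1 vs control, equal AE rates).**
- Extra discontinuation of 0.03 per month in each arm (assumed): 28% to 60%.
- AEs also counted for 28 days after treatment (assumed): 38% to 69%.
- AE hazard confined to the four induction cycles: 3% to 24%. At 0.05 per month, incidence is 10.3% against 11.2% and rejection is 4.6%.
- AE hazard confined to cycle 1: 3% to 5%.

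**Checking the candidate remedies.** A Wald test on first-event rates per patient-month over the whole treatment rejects in 4.9% to 5.1% when the hazard is constant. It fails when toxicity is front-loaded. With equal hazards of 0.05, 0.10, 0.20 and 0.40 per month confined to induction, the whole-treatment rate ratio for arm 1 against control is 0.66 to 0.71, and arm 1 is wrongly called safer in 34%, 52%, 67% and 70% of 10,000 simulated trials. If events and time at risk are both restricted to the induction stage, the ratio is 1.00 and rejection is about 5%.

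**The case against.** The strongest reply is that Fisher's test answers the question the objective asks. The objective is worded in terms of incidence and severity, and the share of patients with at least one event over the regimen as given is a legitimate quantity. That stands. A reader might infer that the safety comparison cannot answer its own question; the documents do not support this. What the test cannot give is a comparison of toxicity rates.

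The test is also conditional on need and sits outside the fixed testing sequence, and Table S3 of the supplement reports counts and percentages without P values. This limits the consequence. It does not remove it, because no condition for using the test is stated.

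Longer treatment in the anlotinib arms is inferred from the PFS hazards and the treat-to-progression rule, not stated, and other reasons for stopping shrink the gap. Chemotherapy is confined to induction and control maintenance is placebo, so a flat hazard is doubtful for chemotherapy toxicity. Where nearly every patient has an event, as with any-grade TEAEs in Table S3 (100% in each arm), the test has nothing to reject. All of this stands and is why the result is given as a range.

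Finally, exposure-adjusted tables are often left to the SAP, which is not shown. Their absence is therefore not the point. The point is that the protocol itself names a test whose P value is open to misreading.

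**Conclusion.** The concern holds in a limited form. For toxicity that continues to arise during maintenance, and for either anlotinib arm against control, a whole-treatment Fisher test can reject well above 5% when the AE rate is equal: about 25% to 77% for arm 1 and 18% to 62% for arm 2 at 0.01 to 0.10 per month. This assumes a constant, equal AE rate, time on treatment equal to planned PFS, and 246 patients per arm. The effect is small to moderate for induction-only toxicity, absent for cycle 1 events, and small for arm 1 against arm 2 (about 4% to 6%), so the comparison that isolates TQB2450 is little affected.

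Two stronger readings might be inferred and are not supported. One is that the test will reject whenever the drug works: the figures are probabilities that depend on an AE pattern the documents do not give. The other is that AE differences between arms in Table S3 are exposure artefacts: that table gives no exposure data, and a true drug effect would look the same. The consequence is for the interpretation of a secondary objective.

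**What to change.** In section 13.5.2:

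- Keep the crude n (%) tables. Label any whole-treatment Fisher P value as comparing whole-regimen incidence, not toxicity rate.
- For TEAEs, grade 3 or higher TEAEs, SAEs and events of special interest, add first-event rates per patient-month with a rate ratio and 95% CI, separately for the induction stage (first four cycles) and the maintenance stage. Cumulative incidence over a common window is an acceptable alternative.
- Do not replace the crude comparison with one whole-treatment rate. When toxicity is front-loaded, that rate favours the longer-treated arm.

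The cost is wording and one more set of safety tables. AE start dates (10.3) and treatment duration (13.5.1) are already collected. Maintenance-stage rates include only patients who reach maintenance, so they should be read as descriptive rather than as a fully randomised comparison.
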